The results of Part 1 of Study DS5670-146 (a phase I/II/III study to evaluate the effect of booster immunization with DS-5670a in Japanese subjects aged 18 years and older who have completed initial immunization with approved SARS-CoV-2 vaccines) confirmed that the GMFR of blood neutralizing activity against SARS-CoV-2 (original strain) at 4 weeks after booster immunization in the DS-5670a 60 µg group was higher than that in the comparator group (Comirnaty IM 30 µg group and Spikevax IM 50 µg group), regardless of the type of the vaccine for initial immunization. With regard to safety, there were no deaths, serious adverse reactions, or AEs that led to permanent discontinuation of study treatment, with no clear difference in the incidence proportion of solicited AEs in the DS-5670a 60 µg group compared with the comparator group, which resulted in the selection of 60 µg as the recommended non-inferiority study dose for booster immunization with DS-5670a in adults and elderly people.

The results of Part 2 of the above study showed that the lower limit of the 2-sided 97.5% confidence interval of the ratio (DS-5670a 60 µg group/comparator group) of the GMFR of blood

Confidential

neutralizing activity against SARS-CoV-2 (original strain) at 4 weeks after study drug administration is greater than the non-inferiority margin of 0.67, regardless of the type of the vaccine for initial immunization, which verified the non-inferiority of DS-5670a to the comparator. With regard to safety, there were no deaths or AEs that led to permanent discontinuation of study treatment, with no clear difference in the incidence proportion of solicited injection site AEs, solicited systemic AEs, unsolicited AEs, or SAEs between the DS-5670a group and the comparator group, regardless of the type of the vaccine for initial immunization.

Based on the study results, 60 µg was also selected as the dose of DS-5670d for this study.

Since the storage, preparation procedures, and dose of DS-5670d and Comirnaty RTU IM are different, indistinguishability of the study drugs cannot be achieved. Therefore, an observer-blind approach was adopted in this study to eliminate bias to evaluations. In the observer-blind approach, the preparation and administration of the study drug and evaluations will be performed by different persons and the evaluations will be performed in a blinded manner.

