### 6.3 Telephone Contact after Study Drug Administration (Day 8, Day 15, Day 22; Allowance $\pm$ 2 Days)

- 1) The investigator, subinvestigator, or study staff will contact the subject or legal representative by telephone on Day 8, Day 15, and Day 22, and ask about the subject's health status. Records of telephone contact documenting whether or not the contact was made and the date of the contact will be kept. It is also acceptable to ask the subject to return to the study site for health status confirmation.
- 2) Based on the record of telephone contact, the investigator, subinvestigator, or study staff will record whether or not the contact was made and the date of the contact in the eCRF.
- 3) The investigator or subinvestigator will judge if the subject's visit is necessary based on the information collected via telephone contact, and document the judgment in the source document.

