#### 6.5 Follow-up Examination (Day 57 [Allowance $\pm$ 7 Days], Day 85 [Allowance $\pm$ 7 Days], Day 113 [Allowance $\pm$ 7 Days], Day 141 [Allowance $\pm$ 7 Days], and Day 183 [Allowance $\pm$ 14 Days])

The subject will visit the study site on Day 57, Day 85, Day 113, Day 141, and Day 183. The investigator or subinvestigator will perform the following investigations, observations, and examinations, and document them in the eCRF. For subjects aged 12 to 17 years, only subjects who are able to visit the study site will visit the study site on Days 57, 113, and 141. In addition, if a solicited AE is ongoing at the study visit for the post-dose evaluation, the investigator or subinvestigator will confirm the outcome of the solicited AE, and enter the log number, event term and date of outcome of the event in the electronic diary in the eCRF.

- Blood sampling for immunogenicity evaluation
- SARS-CoV-2 antibody test (to be performed at the central laboratory)

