The investigator or subinvestigator will confirm whether any AEs have occurred through medical interviews at study visits, subject's electronic diary, hearing of the subject's condition from the subject by telephone confirmation, etc., during the study, or medical examinations. AEs may be directly observed, reported spontaneously by the subject or legal representative, or found by medical interview at each study visit. The subject and legal representative should be questioned in a general way, without asking about the occurrence of any specific symptoms. The investigator or subinvestigator will evaluate nonserious unsolicited AEs, SAEs, and AEs leading to permanent

Confidential

discontinuation of study treatment or withdrawal from the study, and determine the seriousness, severity, and causality according to the definitions provided in Section 9.3. The evaluation by the investigator or subinvestigator will be clearly recorded in the source documents retained at the study site, with signature of the investigator or subinvestigator.

AEs should always be reported as a diagnosis. When a diagnosis is unavailable, the primary sign or symptom will be reported as the event term with additional details included in the narrative until the diagnosis becomes available. If the signs and symptoms are distinct and do not suggest a common diagnosis, they should be reported as individual entries of AEs.

For events that are serious due to hospitalization, the reason for hospitalization should be reported as SAE (diagnosis or symptom requiring hospitalization). Procedures (treatment and surgery) will not be handled as AEs, with no exception, but the reason for the procedure may be an AE. Pre-planned (before signing the ICF) procedures or treatments under hospitalization for preexisting medical conditions that do not worsen in severity need not be reported as SAEs (see Section 9.3.2 for definitions).

For deaths, after confirming the underlying or immediate cause of death, it should always be reported as an SAE.

Any serious, untoward event that may occur subsequently to the reporting period that the investigator or subinvestigator evaluates as related to the study drug should also be handled and reported as an SAE.

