| Solicited adverse events (AEs)                                                 |                       | ←         | →       |         |         |                    |          |                    |                    |          | (■)                       |
| AEs                                                                            |                       | ←         |         |         | →       |                    |          |                    |                    |          | (■)                       |
| SAEs                                                                           | ←                     |           |         |         |         |                    |          |                    |                    | →        | ■                         |
| Investigation of the onset of COVID-19 b                            |                       | ←         |         |         |         |                    |          |                    |                    | →        | ■                         |
| Prohibition period of other medications and concomitant therapies c | ←                     |           |         |         | →       |                    |          |                    |                    |          |                           |

■: Mandatory, ■: To be performed whenever possible, (■): To be performed depending on the timing of withdrawal from the study.

a: To be performed for women of childbearing potential only.  
b: During the investigation, subjects with symptoms suspected of COVID-19 should be instructed to visit the study site whenever possible and undergo the RT-PCR test using nasopharyngeal swab. For subjects tested for COVID-19 at other medical institutions, the result of the test (eg, RT-PCR, SARS-CoV-2 antigen test) should be obtained at a later date.  
c: Use of SARS-CoV-2 vaccines (including drugs used in the study) will be prohibited during the period from informed consent to 26 weeks after study drug administration.  
d: To be performed for subjects aged 12 to 17 years to the extent possible.

Confidential

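### For ages 12 to 17, three of the five follow-up visits are conditional and no contact replaces a missed one, so SAE and COVID-19 follow-up can become purely passive for up to 14 weeks

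*Protocol*

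**What the plan says.** Section 6.5 of the protocol sets the general rule: "The subject will visit the study site on Day 57, Day 85, Day 113, Day 141, and Day 183". For ages 12 to 17 it then adds that "only subjects who are able to visit the study site will visit the study site on Days 57, 113, and 141". In Table 17.1-1, footnote d sits on the visit row at Weeks 8, 16 and 20 and reads "To be performed for subjects aged 12 to 17 years to the extent possible". Days 85 and 183 carry no such relief.

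Three other sections describe the concession more narrowly. Section 3.1 and section 6.7 relax the immunogenicity sample at those three time points, and section 6.11 relaxes the antibody-test sample. None of them speaks of the visit as such.

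Other scheduled contact stops early. Under section 6.3 the site "will contact the subject or legal representative by telephone on Day 8, Day 15, and Day 22, and ask about the subject's health status", and no later call is scheduled. Section 6.8 ends the electronic diary at the 4-week visit.

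The endpoints run longer. SAEs are collected from consent to Week 26 (sections 2.3.5 and 9.2), and COVID-19 incidence over 26 weeks is a secondary endpoint (section 2.3.2.2). On how events are found, section 9.2 says: "The investigator or subinvestigator will confirm whether any AEs have occurred through medical interviews at study visits". It adds the diary, telephone confirmation and spontaneous reports as further routes.

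**The concern.** The purpose of the adolescent concession appears to be to spare minors visits and needles. As worded in section 6.5 and footnote d, it also removes the occasion on which the site would speak to the family, and asking about SAEs or COVID-19 needs neither a visit nor a blood draw.

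For an adolescent who cannot attend, ascertainment then depends on the family contacting the site unprompted, or on recall months later. An SAE may be learned of late. A COVID-19 case that is never reported adds person-time without an event to the rate per 1000 person-years in section 11.4.2.2 and pulls it down. Section 9.4.2 asks for prompt testing and blood sampling when antibody-dependent enhancement is suspected, which late discovery would frustrate.

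The age group matters too. The DS-5670 studies that the protocol describes with a population were in adults: DS5670-103 and DS5670-146 in people aged 18 and older, and DS5670-116 in healthy adults. The dose rationale in section 3.2 likewise refers to "booster immunization with DS-5670a in adults and elderly people". The adolescent study in section 1.2 concerns the comparator's product family.

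**Working it through.** **Inputs.** Visit days and windows from section 6.5 and Table 17.1-1: Day 57 ± 7, Day 85 ± 7, Day 113 ± 7, Day 141 ± 7, Day 183 ± 14. Conditional for ages 12 to 17: Days 57, 113 and 141. Last scheduled call: Day 22 (section 6.3). Diary end: the 4-week visit, Day 29 (section 6.8).

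**Check of the plan's labels.** Day = 1 + 7 × weeks gives 1 + 7 × 12 = 85 and 1 + 7 × 26 = 183. The Week 4, 8, 16 and 20 labels (29, 57, 113, 141) reproduce in the same way. The protocol states no interval between contacts, so there is no stated gap to reproduce.

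**Scheduled contacts after Day 29.** Adults: 5. An adolescent who misses all three conditional visits: 5 − 3 = 2.

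**Gaps.** Nominal gap = later day − earlier day. Longest gap within windows = (later day + its window) − (earlier day − its window).

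| Interval | Nominal | Window limit |
|---|---|---|
| Adolescent, Day 29 to 85 | 85 − 29 = 56 days | (85 + 7) − 29 = 63 days |
| Adolescent, Day 85 to 183 | 183 − 85 = 98 days (14 weeks) | (183 + 14) − (85 − 7) = 119 days (17 weeks) |
| Adult, longest: Day 141 to 183 | 183 − 141 = 42 days (6 weeks) | (183 + 14) − (141 − 7) = 63 days (9 weeks) |

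The like-for-like comparisons are 98 against 42 and 119 against 63. The adolescent figures assume that both the Day 113 and the Day 141 visits are missed. If only Day 141 is missed, the nominal gap is 183 − 113 = 70 days.

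**What remains in the gap.** Section 9.2 collects SAEs to Week 26 from any source. Section 6.13 tells families to contact the site about suspected symptoms, or if they seek COVID-19 care on their own initiative. Section 6.14 adds infected household members. For an adolescent who misses the visits, all of these start with the family. None is a scheduled enquiry by the site.

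**The case against.** The strongest reply is that this is a deliberate and reasonable concession to minors. Attendance depends on being able to come, so it is not a free choice to skip. The SAE and COVID-19 rows of Table 17.1-1 run unbroken to Week 26, and footnote d is not on those rows. Section 9.2 allows telephone confirmation during the study. Reactogenicity in adolescents is fully covered by the diary, three calls and the Day 29 visit. All of this stands, and it limits the point to the loss of scheduled enquiry.

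A reader might infer more than the documents support:

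- **That surveillance stops for 14 weeks.** It does not. It becomes passive.
- **That adults are asked about COVID-19 at these visits and adolescents are not.** Section 6.5 schedules no explicit COVID-19 question at any age. The visit interview in section 9.2 concerns AEs. A difference in COVID-19 ascertainment by age is possible but not written into the plan.
- **That ongoing solicited AEs would not be closed out.** Section 6.8 states that duty without tying it to Days 57, 113 or 141, section 9.2 requires follow-up to resolution or stability, and Day 85 stays required.
- **That this is the age group with the least prior safety data.** Exclusion criterion 18 refers to trial immunization with DS-5670b and DS-5670a/b, for which the protocol gives no study ages, and the Investigator's Brochure is not at hand. The supportable statement is that this protocol cites no DS-5670 data in ages 12 to 17.
- **That the treatment comparison is biased.** Both arms follow the same rule and age is a stratification factor (section 5.1.2).

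The remaining gap is not answered: no call is scheduled after Day 22, and none is named in place of a missed visit.

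**Conclusion.** The point holds in limited form. Section 6.5 and footnote d make the whole visit conditional for ages 12 to 17, where sections 3.1, 6.7 and 6.11 relax only the samples, and nothing replaces a missed visit. The longest interval between scheduled contacts can reach 98 days against 42 for adults (119 against 63 at the window limits).

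The consequence is possible under-ascertainment of SAEs and COVID-19 to Week 26 in adolescents. The primary and key secondary analyses are at Week 4 and are untouched. How many events might be missed cannot be estimated, because the protocol states neither the number of adolescents nor their expected attendance. The conclusion assumes that sites make no routine calls beyond those the protocol schedules. It is a modest weakness that is cheap to repair.

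**What to change.** In section 6.5 and footnote d of Table 17.1-1, keep attendance and blood sampling at Days 57, 113 and 141 as far as possible for ages 12 to 17. Add that if the subject does not attend, the site telephones the subject or legal representative within the same visit window, using the section 6.3 procedure. The call asks about SAEs and about COVID-19 symptoms or positive tests, and the answers go into the eCRF. For comparability, ask the same questions at the attended follow-up visits for all ages.

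If each missed visit is replaced in this way, the longest nominal gap returns to 42 days (63 at the window limits). The cost is a short amendment, a few eCRF items, brief questions at visits that already take place, and at most three short calls per non-attending adolescent by staff who already make the Day 8, 15 and 22 calls. It adds no visit and no blood draw.

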## 6.6 Withdrawal/Discontinuation

If the investigator or subinvestigator judges that the subject should be withdrawn from the study, the investigator or subinvestigator will perform an interview about AEs and SAEs and an investigation on development of COVID-19, and document them in the eCRF. The following investigations, observations, and examinations will be also performed to the extent possible, and documented in the eCRF. The investigator or subinvestigator should sufficiently explain the need for examinations and observations to the subject and legal representative, and document the subject's informed consent in the source document:

- Blood sampling for immunogenicity evaluation
- Clinical laboratory tests (blood/urine)\*
- Pregnancy test (urine)\*
- SARS-CoV-2 antibody test (to be performed at the central laboratory)

\*1: To be performed only for subjects withdrawn from the study during the observation period.

\*2: To be performed only for women of childbearing potential withdrawn from the study during the observation period.

If the subject is withdrawn from the study during the observation period, the investigator or subinvestigator will confirm that all data in the electronic diary have been transferred and then confirm that the application for data entry has been uninstalled from the electronic diary entry device. If a device has been lent to the subject or legal representative, the investigator or subinvestigator will collect the device.

## 6.7 Blood Sampling for Immunogenicity Evaluation

The investigator or subinvestigator will collect samples for immunogenicity evaluation before study drug administration (Day 1) and at 4 weeks (Day 29), 8 weeks (Day 57), 12 weeks (Day 85), 16 weeks (Day 113), 20 weeks (Day 141), and 26 weeks (Day 183) after study drug administration. However, if subjects are aged 12 to 17 years, the samples will be collected from evaluable subjects only at 8 weeks (Day 57), 16 weeks (Day 113), and 20 weeks (Day 141) after study drug administration.

Samples for immunogenicity evaluation will also be collected at the time of withdrawal from the study, if possible. The investigator or subinvestigator will record whether or not blood sampling was performed, and the date of sampling for measurement of blood neutralizing activity against SARS-CoV-2 in the eCRF. The handling, storage, and shipping of samples are specified in a separately prepared procedure manual.

Residual samples after antibody titer measurement may be used for exploratory studies on the safety information of DS-5670d or the relationship between immunogenicity and study drug administration or be used for future evaluation of analytical procedures. Details are specified in a separately prepared plan. Genome and gene analysis research will not be conducted using the

samples.

### 6.7.1 Sample Handling Methods

Details are specified in a separately prepared procedure manual.

### 6.7.2 Labeling for Sample Storage Containers and Shipment Method

Details are specified in a separately prepared procedure manual.

### 6.7.3 Evaluation Methods

Details are specified in a separately prepared procedure manual.

## 6.8 Electronic Diary

The investigator, subinvestigator, or study staff will distribute the electronic diary account to the subject or legal representative on the day of study drug administration (Day 1). The investigator, subinvestigator, or study staff will ask the subject or legal representative to record the following items in the electronic diary during the period from the day of study drug administration to the visit for the post-dose evaluation at 4 weeks after study drug administration, and regularly check the details of descriptions on the electronic data capture (EDC) system where the relevant data will be transferred and confirm entry compliance and the safety of the subject. If the subject is aged 12 to 17 years, the legal representative will make entries in the electronic diary in principle. However, if the investigator or subinvestigator judges that the subject can comply with the rules of the study and report symptoms, etc., specified in the protocol, the entry by the subject is acceptable. The investigator or subinvestigator will record the person who recorded data in the electronic diary in the eCRF.

At the visit for the post-dose evaluation at 4 weeks after study drug administration or the visit after withdrawal from the study during the observation period, the investigator or subinvestigator will confirm that all data of the electronic diary have been transferred and then confirm that the application for data entry has been uninstalled from the electronic diary entry device of the subject or legal representative. If a device has been lent to the subject or legal representative, the investigator or subinvestigator will collect the device. If a solicited AE is ongoing at the study visit for the post-dose evaluation, the investigator or subinvestigator will confirm the outcome of the solicited AE, and enter the log number, event term and date of outcome of the event in the electronic diary in the eCRF.

<<Items to be recorded on the electronic diary>>

- Axillary body temperature
  - 1) The subject or legal representative will measure the axillary body temperature of the subject every day for 7 days after study drug administration (Day 1 to Day 8) and record the results. If a fever of 37.5°C and higher persists even after an elapse of 7 days since

Confidential

study drug administration, body temperature will be measured and recorded every day until it drops below 37.5°C.

- 2) On the day of the study drug administration (Day 1), the axillary body temperature will be measured once after the study drug administration, within that day. On Day 2 to Day 8, axillary body temperature will be measured once a day. If the body temperature is measured at multiple times a day, the maximal body temperature will be recorded. The temperature should not be taken immediately after eating, exercising, or taking a bath.
- Solicited Injection Site Adverse Events
    - 1) The subject or legal representative will monitor the injection site of the subject every day for 7 days after study drug administration (Day 1 to Day 8). In the electronic diary, the presence or absence of injection site reactions (redness, swelling, induration, pain, warmth, and pruritus) will be monitored and, if present, their severity (see Section 9.3) will be recorded. If redness, swelling, or induration is observed, the long diameter of it will be recorded. If such events persist even after an elapse of 7 days since study drug administration, the monitoring of severity (long diameter) will be continued every day until the symptoms are resolved, and the result will be recorded.
    - 2) On the day of the study drug administration (Day 1), the injection site will be monitored once after the study drug administration, within that day. On Day 2 to Day 8, the injection site will be monitored once a day.
    - 3) If there are any new symptoms of injection site AEs before the visit for the post-dose evaluation at 4 weeks after study drug administration, except for the above period, the onset of the symptoms will be recorded as unsolicited AEs in the electronic diary. The symptoms, date of onset, severity (see Section 9.3), and the date of disappearance will be reported to the personnel during a medical interview or telephone contact.
  - Solicited Systemic Adverse Events
    - 1) The subject or legal representative will monitor the presence or absence of solicited systemic AEs (fever, malaise, headache, rash, and myalgia) of the subject every day for 7 days after study drug administration (Day 1 to Day 8) and, if there are any symptoms, record the symptoms, date of onset, and severity (see Section 9.3). If such events persist even after an elapse of 7 days since study drug administration, the symptoms will be monitored every day until they resolve, and the result will be recorded.
    - 2) On the day of the study drug administration (Day 1), the presence or absence of systemic AEs will be monitored after the study drug administration, within that day. From Day 2 to Day 8, the presence or absence of systemic AEs will be monitored once a day.
    - 3) If there are any new symptoms of systemic AEs before the visit for the post-dose

Confidential

evaluation at 4 weeks after study drug administration, except for the above period, the onset of the symptoms will be recorded as unsolicited AEs in the electronic diary. The symptoms, date of onset, severity (see Section 9.3), and the date of resolution will be reported to the personnel during a medical interview or telephone contact.

- Unsolicited AEs
  - 1) The subject or legal representative will monitor the presence or absence of unsolicited AEs of the subject every day for 28 days after study drug administration (Day 1 to Day 29) and, if there are any symptoms, record the onset of the symptoms.

